#### Predictors and covariates

The primary theoretical-based predictor with prescriptive value (i.e., moderator) is trait self-regulation [119] which we will assess using the 75-item, self-report Behavior Rating Inventory of Executive Functioning - Adult (BRIEF-A) [120]. The BRIEF-A assesses habitual propensity with self-regulating or executive function within the context of everyday life. It is reliably associated with mental health, health behaviors, and physical health parameters [119]. Demographic variables, medication use, and disease characteristics (e.g., symptom severity, chronicity, treatment history, comorbidities) will be explored as general, non-specific predictors with prognostic value. Prescriptive and prognostic variables will be assessed at baseline.

#### Data collection and management

Sources of research material will include clinical data from structured interviews, self-report measures, physician assessments, and audio-recorded treatment sessions which will be used to establish therapist fidelity to treatment protocols. Clinical data will be captured using research electronic data capture (REDCap) software [95]. REDCap is a secure, Health Insurance Portability and Accountability Act compliant, web-based application designed to support data capture for research studies. Data will be collected for research purposes only and only with consent of the study volunteer released to a designated recipient (e.g., physician). Original hard copy source documents will be kept in study binders in locked cabinets or electronically stored on a secure server that will be encrypted and password protected. Data for analysis will be stored on a study-specific, password-protected database using subject numbers without personal identifiers. All data are backed up on external servers on a daily basis to a central secure data serve at UB. Access is password protected at multiple levels and no member of the EPPIC team apart from those with data management responsibility will have access to these passwords. Digital records of sessions will be stored in a secure, password-protected folder on the UB server. For all data, separate, an encrypted file linking names to trial ID will be kept and password-protected.

### Statistical methods

We intend to interview all randomized individuals even if they drop out of treatment permitting straightforward ITT analyses. Missing data will be addressed using full information maximum likelihood (FIML) methods [121]. We expect that missing data are minimized by using electronic data capture systems that enable real-time data monitoring. We will test for attrition bias by comparing baseline scores for those who are lost to follow-up with those who complete follow-up. If analyses suggest missing data that violates missing at randomness, we will use Bayesian estimation or pattern modeling in place of FIML [122].

We will evaluate non-normality, variance heterogeneity, specification error, and outlier effects in all analyses. We generally will rely on robust methods of analysis (e.g., Huber-White robust standard errors in Mplus or bootstrapping) [122]. We will make clustering adjustments as implemented in the Mplus software, as needed. For all multi-item measures, we will evaluate composite reliability [123], concurrent validity, and discriminant validity. We will routinely test for unidimensionality and explore the factor structure of all multi-item scales. These analyses will dictate the formation of latent variables to accommodate variable inter-correlations and collinearity, as necessary. We will adjust for familywise error rates using a Holm-modified Bonferroni method [122, 124, 125] and will compare results with unadjusted contrasts in the spirit of sensitivity analyses.

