### Participants and eligibility criteria

Planned enrollment is 240 adults between ages 18 and 70 (inclusive) of any gender, race, or ethnicity who have been formally assigned a diagnosis of IC/BPS or CP/CPPS (confirmed by a board-certified study urologist or urogynecologist) with clinically significant pelvic pain present for at least 6 months. Table 1 lists the inclusion and exclusion (urologic and general) criteria with corresponding rationales.

**Table 1 Tab1:** Participant inclusion and exclusion criteria

	Rationale

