#### Data analysis: statistical power analysis

The field has generally operationalized a clinically meaningful effect as a Cohen’s *d* of 0.50 or a correlation equivalent to it of 0.23, the latter of which represents about 5% explained variance [126–128]. Rather than framing power analysis as the probability of correctly rejecting a null hypothesis, we approach it in terms of effect size sensitivity. If a minimal clinically meaningful effect size is set at *d* = 0.50, it does not matter if we “miss” effect sizes less than *d* = 0.50 by failing to reject the null hypothesis for them because they are judged to be non-meaningful [129, 130].

Assuming conservatively a 12% failure to assess individuals, our final sample size of complete case data will be about 211 or about 105 per condition. For a traditional single degree of freedom contrast of means to evaluate paths from treatment to mediator and assuming a power of 0.80, the effect size sensitivity for a sample size of 100 per group is a population Cohen’s *d* of 0.39, which represents about 3.5% explained variance. This sensitivity will decrease somewhat if there is clustering, but the decrease will be offset by the use of baseline covariates. For a regression analysis to estimate paths from mediator to outcome with 8 predictors (to account for the simultaneous entry of mediators and covariates to control), and assuming a squared multiple correlation of 0.40, the effect size sensitivity for a given predictor will be the detection of a population coefficient that represents 3% unique explained variance. If we add a cluster adjustment representing an interclass correlation coefficient of 0.10, the sensitivity increases to 5% unique explained variance. These same statements apply for the analysis of moderation. The full information estimation structural equation model (SEM) we reference below will generally have equivalent if not greater statistical power than the above, so they, by definition, are adequately powered [131].

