**Fig. 2 Fig2:**
[figure not shown]
Randomized experimental trial model of mediation analyses

Also of interest in an RET is the significance and magnitude of paths linking each mediator to the outcome. For example, perhaps a path associated with coping flexibility is not significant, suggesting that, contrary to our assumptions, coping flexibility does not meaningfully elicit UCPPS symptom improvement. In this case, we might consider streamlining the program so that it is simpler by eliminating the flexible problem solving. We will conduct state-of-the-art dominance analyses that allow us to order the relative strength of paths from the mediators to the outcome variable [133].

*Analyses for Aim 1:* Evaluate the efficacy of MC-CBT for UCPPS as compared to a nonspecific control intervention (EDU) in relieving pain and related symptoms. *H1a* states: Patients randomized to MC-CBT will show greater global symptom improvement on primary endpoint (CGI) compared to those randomized to EDU. This hypothesis will be tested using a covariate-adjusted single degree of freedom contrasts at each time point (immediate posttest 2 weeks, 3 and 6 months) comparing MC-CBT versus EDU on the full-scale CGI. Standard covariates will include medication history, gender, age, and indicators of symptom severity as measured at baseline. *H1b* states: MC-CBT will be superior to EDU on key secondary endpoints including the severity of pelvic pain and urinary symptoms, and functional impairment at post treatment. The same analytic strategy for H1a will be applied to secondary endpoints. For secondary outcomes, available baseline data will be included as a covariate.

*Analyses for Aim 2:* Evaluate the durability of MC-CBT relative to EDU at 3 months and 6 months following treatment discontinuation. This will be tested using the same approach as Aim 1 that is focused on the immediate posttest but now it will be focused on the time points of 3 months and 6 months, separately. The group differences in effects at one time point can be compared to the group difference at another time point using a single degree of freedom interaction contrast with time as a within-subject moderator, using a robust estimator (e.g., Huber-White or bootstrapping).

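### The missing-data rule replaces FIML on evidence that cannot show a departure from missing at random, and one of its two replacements rests on the same assumption as FIML

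*Protocol article*

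**What the plan says.** All statements are in the Protocol article. The Statistical methods section sets the default: "Missing data will be addressed using full information maximum likelihood (FIML) methods". It names one attrition diagnostic: "We will test for attrition bias by comparing baseline scores for those who are lost to follow-up with those who complete follow-up". The switching rule follows directly: "If analyses suggest missing data that violates missing at randomness, we will use Bayesian estimation or pattern modeling in place of FIML". No missingness model is attached to the Bayesian option, and nothing says which of the two replacements applies when.

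Under Data analysis: analysis of aims (Aim 1), the primary contrast on the CGI is covariate-adjusted: "Standard covariates will include medication history, gender, age, and indicators of symptom severity as measured at baseline". The power section expects some loss: "Assuming conservatively a 12% failure to assess individuals", leaving "our final sample size of complete case data will be about 211 or about 105 per condition". The Discussion counts the missing-data plan among the trial's strengths.

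**The concern.** The rule asks the data to reveal something they cannot reveal, then lets the answer decide which estimator produces the primary result. Two errors follow. A valid FIML analysis can be discarded because dropouts differ at baseline, although MAR permits such a difference and the adjusted model already conditions on baseline severity. And FIML can be kept when dropout depends on unseen outcomes in a way that leaves no trace at baseline.

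The replacement is also uncertain. The two options can rest on different assumptions, and the choice between them is left until attrition has been seen.

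Outcome-linked loss is plausible in this trial. The primary outcome is patient-rated, and participants know their treatment from session 1 (Sequence generation; Blinding). The dropout codes under Retention and compliance include leaving because of feeling better and leaving because treatment did not meet the person's needs.

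**Working it through.** **1. The plan's own figure.** Enrollment is 240 and assumed loss is 12%. 240 × (1 − 0.12) = 211.2, or 105.6 per arm, which agrees with the stated 211 and 105. About 240 × 0.12 = 28.8, or 29 people, would lack outcome data. No stated number is disputed.

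**2. What the observed data can show.** Let Y be the follow-up CGI, X the baseline covariates, T the arm, and R = 1 if Y is observed. The data identify P(R = 1 | X, T) and the distribution of Y given X, T and R = 1. They carry no information on Y given X, T and R = 0. MAR given X and T says that these two distributions of Y are equal.
- A baseline difference between the lost and the completers shows that R depends on X. That contradicts MCAR and is compatible with both MAR and MNAR.
- Any other analysis of observed data meets the same limit, so a wider reading of the trigger does not repair it.

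**3. What the replacements assume.** Bayesian estimation with no model for R uses the same ignorable likelihood as FIML, plus priors. With vague priors it gives practically the same answer. Pattern modeling can let the missing Y differ from the observed Y by a stated amount, so it can address MNAR.

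**4. Simulation.** From the document: N = 240, 1:1 allocation, 12% missing, and d = 0.50 (its clinically meaningful effect) taken as the true effect. Assumed: baseline–outcome correlation 0.4, the dropout slopes, and a 25% missing case.
- Outcome: Y = 0.50·T + 0.4·X + e, with Var(e) = 1 − 0.4² = 0.84 and higher values better, so bias is in within-arm SD units.
- Dropout: logit P(missing) = c + f, with c set to give the overall rate.
- Flag: Welch t-test of X by dropout status at p < 0.05.
- Estimators: regression of Y on T and X in observed cases (equal to ML under MAR when only Y is missing), and a Bayesian fit of the same likelihood with vague priors.
- 3,000 trials per row; Monte Carlo SE of the bias 0.002–0.003.

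| Dropout mechanism | f | Flagged, 12% | ML bias, 12% | Bayesian bias, 12% | Flagged, 25% | ML bias, 25% |
|---|---|---|---|---|---|---|
| MCAR | 0 | 5.5% | −0.003 | −0.003 | 5.3% | 0.004 |
| MAR, on baseline | 1.0·X | 99.4% | 0.000 | 0.000 | 100% | 0.005 |
| MNAR, poor residual outcome, CBT arm only | −1.5·T·e | 5.1% | +0.150 | +0.150 | 5.5% | +0.268 |
| MNAR, residual, opposite by arm | −1.5·(2T − 1)·e | 4.9% | +0.249 | +0.249 | 5.3% | +0.482 |
| MNAR, outcome itself, both arms | −1.5·Y | 65.6% | −0.058 | −0.058 | 84.2% | −0.094 |

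ML and Bayesian estimates agreed to within 0.001 in every row, at 25% as well. The third row inflates the effect by 0.150/0.50 = 30%. The last row is flagged only because Y correlates with X, a pattern that MAR also produces.

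**5. Other assumptions.**
- True d = 0.39, baseline–outcome correlation 0.3, 2,000 trials. Outcome-residual dropout in the CBT arm (9% missing) was flagged in 6% of trials with bias 0.09. Baseline-driven dropout (12% missing) was flagged in over 99% with bias below 0.01. The dropout slope for this run is not available, so it supports direction only.
- A further run at about 12% missing (correlation 0.4, d = 0.50). The CBT-arm mechanism was flagged in about 5% of trials with bias 0.10 to 0.17. Dropout on the outcome in both arms was flagged in 39–66%.

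**The case against.** **The trigger is inferred.** The baseline comparison and the switching rule are separate sentences, and the second refers only to analyses in general. A reader might infer that the baseline test is the stated and sole trigger. The text does not say so; it is the only diagnostic named and comes immediately before the rule. The firing rates above depend on that reading. The limit in step 2 does not.

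**Pattern modeling is offered.** A reader might infer that neither replacement handles MNAR. That is wrong, since pattern modeling can. Bayesian selection models also exist, and the source cited for the rule cannot be consulted here. What stands is that the article states no such model, so the rule permits the ignorable version.

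**The rule is not always blind.** When dropout follows the outcome in both arms, the test flags often (65.6% at 12% missing). It would be too strong to say that it stays silent whenever FIML is biased.

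**The analysis plan is not shown.** A reader might infer that no MNAR sensitivity analysis is planned. An article commonly leaves that detail to the SAP, so its absence is not part of this point. The stated conditional rule is.

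**Bias may be smaller.** The CGI is also collected during treatment. In a simulation with 12% missing per arm, dropout slope 1 and an assumed 0.7 residual correlation between interim and final CGI, using the interim CGI in the likelihood cut the bias from 0.10 to 0.05. When dropout followed observed interim non-response, it fell from 0.08 to 0.01. The article does not say that interim CGI enters the primary likelihood, so this is possible mitigation only.

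**Safeguards exist.** FIML is already the default, treatment dropouts are to be interviewed, and 12% is described as conservative. Masked physicians also rate the CGI, but at the same follow-ups, so those ratings may well be missing for the same people. These points limit the size of the problem and leave the rule's logic unchanged.

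**Conclusion.** The point holds in a bounded form. The rule rests on a determination that observed data cannot supply. The one diagnostic named bears on MCAR, and one of the two permitted replacements shares FIML's assumption unless a non-ignorable model is added. It can therefore discard a valid primary analysis, and it can miss outcome-driven dropout that is unrelated to baseline.

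The sizes (about 5–6% flagged and roughly 0.09–0.17 SD of bias at 9–12% missing) are illustrative. They rest on an assumed dropout strength and baseline–outcome correlation, neither of which the document gives, and on dropout in one arm that leaves no trace at baseline. The logical conclusion needs none of these assumptions.

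This should be fixed before outcome data are examined by arm, because the rule decides which estimator yields the primary result. It does not undermine the design, the data collection or the default analysis.

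**What to change.** Replace the switching rule with four statements:

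1. The likelihood analysis under MAR (FIML) is primary whatever the attrition comparison shows.
2. The comparison of baseline scores is descriptive and guides the choice of auxiliary variables.
3. The pattern-modeling option becomes a prespecified MNAR sensitivity analysis that always runs: delta-adjusted or pattern-mixture shifts of missing CGI, separately by arm, over a stated range up to the tipping point. For scale, with 12% missing in an arm, a shift of δ SD in its missing values moves that arm's mean by 0.12·δ SD.
4. Bayesian estimation is removed as a response to MNAR unless an explicit non-ignorable model and its priors are specified.

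The cost is one paragraph of text and one extra analysis, with no new data.

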#### Data analysis: statistical power analysis

The field has generally operationalized a clinically meaningful effect as a Cohen’s *d* of 0.50 or a correlation equivalent to it of 0.23, the latter of which represents about 5% explained variance [126–128]. Rather than framing power analysis as the probability of correctly rejecting a null hypothesis, we approach it in terms of effect size sensitivity. If a minimal clinically meaningful effect size is set at *d* = 0.50, it does not matter if we “miss” effect sizes less than *d* = 0.50 by failing to reject the null hypothesis for them because they are judged to be non-meaningful [129, 130].

Assuming conservatively a 12% failure to assess individuals, our final sample size of complete case data will be about 211 or about 105 per condition. For a traditional single degree of freedom contrast of means to evaluate paths from treatment to mediator and assuming a power of 0.80, the effect size sensitivity for a sample size of 100 per group is a population Cohen’s *d* of 0.39, which represents about 3.5% explained variance. This sensitivity will decrease somewhat if there is clustering, but the decrease will be offset by the use of baseline covariates. For a regression analysis to estimate paths from mediator to outcome with 8 predictors (to account for the simultaneous entry of mediators and covariates to control), and assuming a squared multiple correlation of 0.40, the effect size sensitivity for a given predictor will be the detection of a population coefficient that represents 3% unique explained variance. If we add a cluster adjustment representing an interclass correlation coefficient of 0.10, the sensitivity increases to 5% unique explained variance. These same statements apply for the analysis of moderation. The full information estimation structural equation model (SEM) we reference below will generally have equivalent if not greater statistical power than the above, so they, by definition, are adequately powered [131].

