### Sequence generation, concealment, and implementation

Simple randomization into one of the two equal-probability conditions in a 1:1 ratio on a continuous basis as participants qualify for allocation will be performed by the study coordinator who has no patient care responsibilities as a safeguard against selection bias. In addition, treatment assignment will be conducted using Randomization Module in Research Electronic Data Capture (REDCap) software [95], which *generates* random and unpredictable sequence of assignments. The details of its computer-generated randomization algorithm are unknown to members of the EPPIC research team. Allocation sequence *concealment* from study personnel is achieved because REDCap conceals the next treatment assignment from being known. In other words, neither participants nor members of the research team are aware of the generated sequence until (and only for) the participant is assigned to his/her respective condition. Allocation sequence is generated by a computer independent of research coordinator who *implements* the assignment. Because the two treatments have identical dosages (4 sessions), the condition to which the participant is assigned is not revealed to him/her until session 1 of the acute phase, further minimizing selection bias.

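### The power section equates d = 0.50 with r = 0.23 and about 5% of variance (it is r = 0.24 and 5.9%), and its 3% regression sensitivity does not reproduce; both slips are conservative

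*Protocol article*

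**What the plan says.** All the figures are in the Protocol article, under the heading Data analysis: statistical power analysis, unless noted.

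- **Threshold.** The opening sentence reports how the field usually defines a clinically meaningful effect: d = 0.50, "or a correlation equivalent to it of 0.23, the latter of which represents about 5% explained variance". The section then adopts the d value for its own argument ("If a minimal clinically meaningful effect size is set at *d* = 0.50") and accepts missing anything smaller.
- **Sample.** "Assuming conservatively a 12% failure to assess individuals, our final sample size of complete case data will be about 211 or about 105 per condition". This starts from the 240 given under Participants and eligibility criteria.
- **Mean contrast.** With 100 per group and "assuming a power of 0.80", the sensitivity is d = 0.39, put at about 3.5% of variance.
- **Regression path.** With 8 predictors and a model R² of 0.40, "the effect size sensitivity for a given predictor will be the detection of a population coefficient that represents 3% unique explained variance".
- **Clustering.** With an intraclass correlation of 0.10, "the sensitivity increases to 5% unique explained variance".

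Allocation is described under Sequence generation, concealment, and implementation: "Simple randomization into one of the two equal-probability conditions in a 1:1 ratio". The power section states no alpha or sidedness, and does not repeat the power or the N for the regression.

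**The concern.** The section deliberately replaces a conventional power statement with a comparison of detectable effects against a threshold. For the mediator and moderator regressions, that comparison can be made only on the variance scale, because the sensitivities there are given as percentages of variance. The conversion of d = 0.50 to a percentage, and the 3% itself, therefore carry the printed argument for those analyses. If either figure is off, a reader cannot tell how much margin the design has. The section also extends the same figures to moderation.

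**Working it through.** **Inputs.** Threshold d = 0.50; stated equivalents r = 0.23 and about 5%; 1:1 allocation; N = 200 (100 per group) or 211 (240 × 0.88 = 211.2); 8 predictors; R² = 0.40; power 0.80. Alpha is not stated, so two-sided 0.05 is assumed and tested in step 2.

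**1. Conversion of the threshold.** For equal groups, r = d/√(d² + 4).

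- d = 0.50: r = 0.50/√4.25 = 0.2425, and r² = 0.0588, or 5.9%.
- r = 0.23: r² = 0.0529, or 5.3%, and d = 2 × 0.23/√(1 − 0.0529) = 0.473.
- r² = 0.05: r = 0.2236 and d = 0.459.

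So 0.23 and about 5% agree with each other within rounding, but not with d = 0.50. Two possible explanations were tried:

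- *Unequal arms.* r = 0.23 from d = 0.50 would need a split of about 34:66, which 1:1 allocation does not give.
- *Shrunken R².* At N = 200, d = 0.50 shrinks to 1 − 0.9412 × 199/198 = 5.4%, which is r of about 0.23. The same shrinkage takes d = 0.39 to 1 − 0.9634 × 199/198 = 3.2%, whereas the section prints about 3.5%. Unshrunken, d = 0.39 is 0.1521/4.1521 = 3.7%. Shrinkage therefore does not account for both statements.

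**2. The plan's d = 0.39, and the alpha it implies.** Two-sample noncentral t, 80% power:

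| Setting | Detectable d, 100 per arm | Detectable d, 105 per arm |
|---|---|---|
| two-sided 0.05 | 0.398 | 0.388 |
| one-sided 0.05 | 0.353 | 0.344 |

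At 100 per arm, d = 0.39 has 78% power two-sided. The printed 0.39 is thus reproduced, to rounding, by two-sided 0.05 and 80% power. One-sided testing does not reproduce it.

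**3. The 3% regression sensitivity.** Noncentral F with 1 numerator df and N − 9 denominator df; f² = ΔR²/(1 − 0.40); λ = f² × N. For 80% power at two-sided 0.05:

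- N = 200: f² = 0.0396 (λ = 7.92), so ΔR² = 0.60 × 0.0396 = 0.0238, or 2.4%.
- N = 211: f² = 0.0376 (λ = 7.93), so ΔR² = 0.0225, or 2.25%.

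Taking 3% as given, f² = 0.03/0.60 = 0.05. Then λ = 10.0 at N = 200 (power 0.882) and 10.55 at N = 211 (power 0.898).

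**4. Settings that do return 3%.**

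- 90% power, N = 211: 3.02%. The mean contrast would then be (1.960 + 1.282) × √(2/n), giving d = 0.46 at 100 per arm and 0.45 at 105.
- Alpha 0.0167, 80% power, N = 211: 3.02%. The mean contrast would be (2.394 + 0.842) × √(2/n), again 0.46 and 0.45.
- One-sided 0.05, N = 200, read as partial R²: 3.02%. This needs d of about 0.35 for the mean contrast, and a quantity other than the unique variance that is printed.

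None of these also gives d = 0.39.

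**5. The clustered 5%.** Design effect = 1 + (m − 1) × 0.10 for m patients per cluster. With m = 12 it is 2.1, and 2.4% becomes 5.1% at N = 200 (4.8% at N = 211). Starting from 3%, a ratio of 5/3 = 1.67 corresponds to m of about 8. The 5% can therefore arise from the recomputed value or from the 3%; the article does not show which.

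**The case against.** The strongest reply is that nothing depends on these slips. The plan adopts one threshold, d = 0.50, and r = 0.23 with about 5% appears only in a sentence about what the field does, supported by citations. A 5% benchmark is stricter than 5.9%, and 3% claims less sensitivity than the design has. In addition, alpha is unstated and power is not repeated for the regression, while the Statistical methods section plans a Holm-type adjustment, so a smaller alpha behind the 3% is possible.

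Most of this stands, and it rules out several stronger readings that a reader might infer:

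- *Three competing thresholds.* Not supported. There is one threshold, and its two variance-scale equivalents agree with each other; they are simply a poor conversion of d = 0.50.
- *Clustered sensitivity only ties with the threshold.* The tie comes from the conversion. Against 5.9% the stated 5% has room.
- *The 5% carries the 3% error forward.* Not shown. About 12 patients per cluster takes 2.4% to about 5%.
- *The cluster size is a missing item.* An article commonly leaves this to the full protocol or analysis plan.

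What the reply does not remove is that d = 0.50 and r = 0.23 are called equivalent and, under 1:1 allocation, are not. Nor does an adjusted alpha or higher power rescue the 3% without contradicting the d = 0.39 in the same paragraph, unless the two figures were computed under different settings that the text does not declare.

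**Conclusion.** The point holds as a correction of printed figures and no more. The conversion is off by 0.013 in r and by about 0.9 percentage points of variance (0.6 against the unrounded 5.3%). The regression sensitivity is printed as 3% where the implied setting gives 2.4% (N = 200) or 2.25% (N = 211). The second result assumes two-sided 0.05 and 80% power; the article does not state these for the regression, but its own mean-contrast figure implies them.

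Both slips are conservative. The stated sensitivities of about 3.5%, 3% and, with clustering, 5% meet the threshold under either conversion. A reader might infer that the trial is underpowered or that 240 is the wrong number; the documents do not support that, and neither the sample size nor the adequacy conclusion changes. The importance is minor.

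**What to change.** 1. Restate the threshold as d = 0.50, r about 0.24, about 6% of variance.
2. Restate the regression sensitivity as about 2.4% unique variance at N = 200 (two-sided 0.05, 80% power). If 3% was intended, give the different alpha or power that produces it.
3. Check that the clustered 5% follows from the restated value, and amend it if it does not.

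The cost is a few edited figures. Design, sample size and planned analyses are untouched.
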